## **9.5 Withdrawal of individual subjects**

Subjects can leave the study at any time for any reason if they wish to do so without any consequences. The investigator can decide to withdraw.

### **9.5.1 Specific criteria for withdrawal of individual subjects**

Protocol therapy will be discontinued at any time if the following situations occur:

- the development of symptoms which, in the investigator's judgment, preclude further therapy;
- subject withdrew consent;
- lost to follow-up;
- pregnancy;
- study termination;
- the development of severe renal impairment (creatinin > 177 µmol/l).

### **9.5.2 Replacement of individual subjects after withdrawal**

Subjects withdrawn from treatment will not be replaced with other subjects.

### **9.5.3 Follow-up of subjects withdrawn from treatment**

All efforts will be made to follow the patient until the end of the study according to the study schedule. Patients withdrawn from the study will retain their patient number and their medication code already allocated.

## **10. SAFETY ASPECTS AND SAFETY REPORTING**

### **10.1 Safety aspects**

#### **10.1.1 Metformin**

To decrease the risk of lactic acidosis, strict prescribing guidelines for metformin therapy have been developed. Absolute contraindications include renal insufficiency (creatinin > 177 µmol/l) and metabolic acidosis. Metabolic acidosis caused by metformin only occurs in case of impaired renal function (creatinin > 177 µmol/l). Therefore, renal function will be monitored. In case of renal function deterioration (creatinin > 177 µmol/l), pH and lactate levels will be determined. Relative contraindications include conditions associated with hypoxemia and hypovolaemia. In addition, the incidence of lactic acidosis has been reported only during chronic administration of metformin (measured in patient-years), which makes it difficult to quantify the risk for lactic acidosis in patients undergoing a specific, high-risk event, such as PCI.

#### **10.1.2 PCI procedure**

PCI will be performed according to current European and U.S. guidelines.

### **10.2 Medical Research Involving Human Subjects Act (WMO) event**

In accordance to section 10, subsection 1, of the Medical Research Involving Human Subjects Act (WMO), the investigator will inform the subjects and the reviewing accredited Medical research ethics committee (METC) if anything occurs, on the basis of which it appears that the disadvantages of participation may be significantly greater than was foreseen in the research proposal. The study will be suspended pending further review by the accredited METC, except insofar as suspension would jeopardize the subjects' health. The investigator will take care that all subjects are kept informed.

### 10.3 Adverse and serious adverse events

Adverse events are defined as any undesirable experience occurring to a subject during a clinical trial, whether or not considered related to the investigational procedure. All adverse events reported spontaneously by the subject or observed by the investigator or his staff will be recorded. Disease related adverse events, which are clearly related to the underlying condition of the patient and are not related to the intervention, will only be reported 6 monthly to the METC.

A serious adverse event is any untoward medical occurrence or effect that:

- results in death;
- is life threatening (at the time of the event);
- requires hospitalization or prolongation of existing inpatients' hospitalization;
- results in persistent or significant disability or incapacity;
- is a new event of the trial likely to affect the safety of the subjects, such as an unexpected outcome.

Since metformin is a widely used medicine which adverse effects have been described in detail, serious adverse events which are common in patients suffering from myocardial infarction which have no known association with the intervention ("disease related adverse events") will be reported 6 monthly to the METC. All serious adverse events with a known association with metformin will be reported to the accredited METC that approved the protocol, according to the requirements of that METC. Serious adverse events that are used to assess safety by the DSMB, which include death, re-MI, target vessel revascularization, worsening renal failure and lactic acidosis will be reported to the METC at all times.

Subjects transferred to other hospitals (referring hospitals) after PCI, which is standard care, will not be considered as an SAE. For logistical reasons, the discharge date from the UMCG will be used to plan the subsequent study visits (T1 – T5). The actual dates that the patients are discharged from the referring hospitals will be collected afterwards and recorded in the database as date of discharge.

#### 10.4 Follow-up of adverse events

All adverse events will be followed until they have abated, or until a stable situation has been reached. Depending on the event additional tests, medical procedures as indicated or referral to a general physician or medical specialist according to current guidelines, possibly resulting in treatment, will take place. Participation in this trial will not interfere with treatment of adverse events.

#### 10.5 Data Safety Monitoring Board

A DSMB is established to perform ongoing safety surveillance and to perform interim analyses on the safety data. This committee is an independent committee, consisting of:

- [name], PhD, epidemiologist (Chair);
- [name], MD PhD, Interventional cardiologist (member);
- [name], MD PhD, Cardiologist (member);
- [name], MD, hospital pharmacist, epidemiologist (member);
- [name], MD, endocrinologist (member).

These members have no conflict of interest with the sponsors of the study. The DSMB will meet on regular basis (i.e. 2-3 times per year) to evaluate (serious) adverse events, drug safety and clinical endpoints. The charter of the DSMB is added as an attachment (see attachments).

Extending recruitment (based on actual control arm response rates being different to predicted rather than on emerging differences) will be recommended by the DSMB based on the conditional power analysis that will be performed after 280 patient have reached their primary endpoint (LVEF analysis by CMR imaging 4 months after randomization) based on actual control arm response rates being different to predicted rather than on emerging differences. The maximal number of patients to which the inclusion can be extended in this trial will be limited to 450.

## 10.6 Monitoring

The monitoring of the GIPS-III trial will be performed by the Trial Coordination Center. They will monitor the trial according to the monitor plan; i.e. monitor the database and monitor patient safety according to the current NFU Guidelines (Nederlandse Federatie van Universitair Medische Centra).

## 10.7 Endpoint Adjudication Committee (EAC)

In order to reduce bias and discrepancies in the judgment of the investigators and to increase accuracy in the assessment of clinical endpoints, an Endpoint Adjudication Committee is established.

All endpoints reported in the GIPS-III trial have to be assessed by the EAC. The EAC has to determine whether the investigators assessment of the endpoint is correct and complete. If not, the EAC will adjudicate the assessment of the investigators. The investigators will have to adopt the assessment by the EAC.

This committee is an independent committee, consisting of:

- [name] [name], MD, PhD (cardiologist, Chair)
- [name], MD, PhD (Interventional cardiologist, member)
- [name] [name], MD, PhD (internist-endocrinologist)

The assessment of the endpoints is particularly important for the analyses performed by the Data and Safety Monitoring Board (DSMB) of the GIPS-III trial. The DSMB advises the sponsor and steering committee of the GIPS-III trial regarding safety of trial participants and those yet to be recruited. Furthermore, the DSMB advises the sponsor and steering committee of the GIPS-III trial about the validity and scientific merit of the GIPS-III trial.

In order to provide the DSMB with objective and accurate information about endpoints, the investigators of the GIPS-III trial need to provide objective and definitive conclusions on events and

endpoints reached in the trial. The EAC is responsible for the assessment of these endpoints, which the DSMB will use for their analyses.

## **11. STATISTICAL ANALYSIS AND SAMPLE SIZE**

### **11.1 Statistical analysis**

Analyses will be performed according to the intention-to-treat principle for the whole population and in the specified subgroups. An analysis per protocol will also be performed. Differences between group means will be assessed with the two-tailed Student's t-test. Chi-square analysis or Fisher's exact test is used to test differences between proportions. Survival will be calculated by the Kaplan-Meier product-limit method. The Mantel-Cox (or log-rank) test will be used to evaluate differences in survival between the two treatment groups. The Cox proportional-hazards regression model will be used to calculate relative risks and to adjust for differences in baseline characteristics. The relationship between metformin use and the primary and secondary endpoints will be studied using linear regression analysis, in which the outcome at the time of determination will be adjusted for the outcome at baseline. In addition, to assess the relationship between the determinant and the outcome over multiple measurements in time, GEE (generalized estimation equations) will be used as a method for dealing with correlated data arising from repeated measurements. Statistical significance is considered as a two-tailed p value <0.05. The Statistical Package for the Social Sciences (SPSS Inc., Chicago, IL, USA) version 16.0 will be used for all statistical analysis.

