## **9.2 Subgroups**

The primary and secondary endpoints will be analyzed in prespecified subgroups defined by:

- gender;
- age;
- BMI;
- location of myocardial infarction;
- physical diagnostics;
- ECG characteristics;
- laboratory findings;
- CMR-imaging findings.

Furthermore, we will perform “per protocol” analyses restricted to compliant patients and who did not receive ‘open label’ anti-hyperglycaemic strategies for clinical reasons (e.g. developed diabetes during the study).

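### Subgroup analysis repeats the two-arm tests at p<0.05 inside each stratum, with no stated comparison between strata and three "prespecified" classes that name no variable

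*Protocol*

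**What the plan says.** Protocol 11.1 sets the scope: "Analyses will be performed according to the intention-to-treat principle for the whole population and in the specified subgroups". It then lists the methods. For continuous outcomes, "Differences between group means will be assessed with the two-tailed Student's t-test". Proportions are compared by chi-square or Fisher's exact test and survival by the log-rank test. Cox regression, linear regression adjusted for the baseline value, and GEE are also named. A single criterion follows: "Statistical significance is considered as a two-tailed p value <0.05".

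Protocol 9.2 says which endpoints are involved: "The primary and secondary endpoints will be analyzed in prespecified subgroups defined by" eight headings. Gender, age, BMI and "location of myocardial infarction" are recognisable factors, although age and BMI have no cut-points. Three others, "physical diagnostics", "ECG characteristics" and "laboratory findings", name no variable, cut-point or time of measurement. The eighth, CMR findings, raises a different question because CMR is done only at 4 months. It is not part of this point.

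**The concern.** A test within a stratum asks whether metformin differs from placebo in that stratum. It does not ask whether the effect differs between strata, which is the usual purpose of a subgroup analysis. The trial is sized for the whole sample, so each stratum test is underpowered. One stratum will often be significant and its complement not, even when the true effect is identical in both. Such a pair of results looks like effect modification. If LVEF is neutral overall, a stratum that crosses 0.05 by chance could be presented as a positive finding. This matters in a proof-of-concept trial (11.3), whose results may guide whom to study next.

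The open classes add to the problem. Section 9.1.3 lists more than a dozen laboratory measures, some groups ending in an open etcetera, taken before discharge and at each outpatient visit. Section 9.3.3 schedules ECGs at presentation, after PCI, before discharge and at each visit. Section 9.4 repeats the clinical examination at each visit. Study drug starts within 3 hours after PCI (5.1), so many of these values are post-treatment. Many different splits, some of them on variables that treatment may have changed, could later be described as prespecified.

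**Working it through.** **Inputs.** Difference 3 LVEF points, SD 9, two-sided α 0.05, power 80%, 141 per arm and 282 evaluable (11.3 and 11.3.1); 380 randomised with 26% unscanned (11.3.1). Assumed here, because the protocol gives nothing: binary factors, independent of each other, split 50:50 unless stated.

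**1. The protocol's own figure.** N = (1.96 + 0.84)² × 2 × 9²/3² = 7.84 × 18 = 141.1 per group, which agrees with 141. Power at 141 per arm is 79.9%. Also 380 × 0.74 = 281 scans, which agrees with 282.

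**2. Power inside one stratum.** A 50:50 split leaves 70.5 per arm. SE = 9 × √(2/70.5) = 1.516. Power ≈ Φ(3/1.516 − 1.96) = Φ(0.019) = 0.508.

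**3. Discordant strata for one factor, identical true effect.** The strata contain different patients, so P(exactly one significant) = 2 × 0.508 × 0.492 = 0.50. With a 75:25 split the stratum powers are 0.679 and 0.288, giving 0.679 × 0.712 + 0.288 × 0.321 = 0.58.

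**4. Several factors.** The same patients are re-cut for each factor, so the results are correlated and simulation is needed (282 patients, 4,000 to 8,000 trials per scenario).

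| True uniform effect | Factors | At least one discordant factor | At least one significant stratum |
|---|---|---|---|
| 3 points | 1 | 0.50 | 0.75–0.76 |
| 3 points | 4 | 0.80–0.81 | 0.90–0.91 |
| 3 points | 8 | 0.88–0.89 | 0.94–0.95 |
| 2 points | 4 | 0.67 | 0.69 |
| 1 point | 4 | 0.39 | 0.39 |
| 1 point | 8 | 0.52 | 0.53 |
| none | 4 | 0.24 | 0.25 |
| none | 8 | 0.36 | 0.37 |

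Uneven splits for four factors (75, 50, 50 and 40%) gave 0.84 discordant at 3 points and 0.25 for any significant stratum under no effect.

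**5. The like-for-like comparator.** A uniform effect cancels from the difference between strata, so an interaction test keeps its 5% level whatever that effect is. Over four independent factors, 1 − 0.95⁴ = 0.185 (simulated 0.18 to 0.19). Over eight, 1 − 0.95⁸ = 0.34 (simulated 0.34). The fair comparisons at 3 points are therefore 0.50 with 0.05 for one factor, and about 0.80 with 0.19 for four.

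**6. What interaction tests do not fix.** Under no effect with four factors, the chance of at least one nominal signal falls only from 0.25 to 0.19. The multiplicity across factors remains, so an exploratory label is needed as well.

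**7. Power of the interaction test.** For a 50:50 factor the SE of the difference between strata is 1.516 × √2 = 2.144. A true difference of 3 points between strata is detected with probability Φ(3/2.144 − 1.96) = Φ(−0.561) = 0.29.

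**The case against.** The strongest reply is that this is mainly silence. Interaction terms, cut-points and exploratory labels are commonly left to a statistical analysis plan, which is not shown here. Section 11.1 also names linear and Cox regression, the models in which an interaction term would sit, so nothing excludes one. That part stands: absence of an interaction test alone would be no finding. What remains is that 9.2 and 11.1 positively direct the two-arm analyses, under the 0.05 criterion, into the subgroups, and call prespecified three classes that are not specified. A later plan could add to that text, but the text itself would still need correcting.

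Three stronger readings are tempting and are not supported.

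- A reader might infer that false subgroup findings are more likely than not whenever metformin acts equally in everyone. For LVEF this needs a true effect near the design value or many factors. With no effect the chance is 25 to 37% for four to eight factors, and with a 1-point effect and four factors it is about 38 to 39%.
- A reader might infer that the protocol tells the analyst to conclude effect modification when one stratum is significant and the other is not. It fixes no such rule. With a real uniform effect the significant stratum is a true positive, and the error lies in how the contrast is read.
- A reader might take the 25% under no effect as breaching a promised 5%. Section 11.1 states a per-test threshold and makes no family-wise claim.

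It is also fair to say that no sample-size, stopping or success decision in the protocol depends on a subgroup.

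**Conclusion.** The point holds in this limited form. The stated subgroup method answers the wrong question, and three of the listed factors are not prespecified in any usable sense. At the protocol's own design values, discordant strata would arise by chance in about half of trials for one evenly split factor and in about 80% for at least one of four. Interaction tests would give about 5% and 19%. The size depends on the true effect (about 38 to 39% for four factors at 1 point) and on the assumption of independent binary factors. Uneven splits raise the discordance, and open-ended classes add factors. With no true effect, about one trial in four would show at least one stratum of four factors at p<0.05 on LVEF alone. The intention-to-treat comparison of LVEF in the whole population is not affected. The change should be made, because subgroup statements produced under the present wording would be unreliable.

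**What to change.** In 9.2 and 11.1, state that:

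- differences in treatment effect between subgroups are assessed by a treatment-by-subgroup interaction term, in the linear model for LVEF and in a Cox or logistic model for events;
- stratum estimates with 95% CI are descriptive;
- all subgroup results are exploratory.

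Keep sex, age, BMI and infarct location, with age and BMI either modelled continuously or given cut-points fixed before unblinding. Delete the three open classes, or replace each with named variables measured before the first dose. The ECG at presentation (9.3.3) and the admission blood sample (7.2) are possible sources.

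The cost is a few sentences and one model term per factor, using data already collected. The drawback is low power: about 29% for a true 3-point difference between equal strata. Stratum-level significance could also no longer be claimed.

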Infarct size after myocardial infarction is comparable in patients with and without diabetes (2;13). However, patients with diabetes have a lower left ventricular ejection fraction (LVEF) (6) and more congestive heart failure after myocardial infarction (2). Left ventricular dysfunction in diabetics is not only caused by decreased systolic ventricular function. Diabetic patients have higher diastolic stiffness of the left ventricle, contributing to the decreased ventricular function in diabetics (14). Therefore, the decreased systolic and diastolic ventricular function and increased congestive heart failure observed in diabetes is apparently not the result of more ischemic injury. The decreased LVEF can be the result of glycometabolic disturbances, including an increased utilization of free fatty acids, and impaired pre-conditioning causing myocardial cells to be more prone to ischemic and reperfusion injury (2). Patients with diabetes have decreased myocardial flow reserve, which is related to long-term glucose dysregulation (2). The presence of multi-vessel disease is also associated with a limited recovery of myocardial function after MI. Extensive coronary artery disease, autonomic dysfunction and a high prevalence of hypertension and dyslipidemia have all been linked to the increased susceptibility of diabetic patients to develop heart failure (2). Furthermore, endothelial dysfunction resulting in increased vascular resistance, is not only associated with congestive heart failure but also with diabetes and glucose disturbances in the sub-diabetic range (3). Diabetic cardiomyopathy, which is induced by various mechanisms, also predisposes to heart failure.

Besides the left ventricular function, pro-thrombotic disturbances in the coagulation system and a higher prevalence of co-morbidity such as renal disease may also contribute to the adverse prognosis of diabetic patients.

Renal function is associated with mortality and hospitalization in patients with heart failure (15). Worsening renal function is a predictor for mortality and hospitalization (16), both in- and out-

hospital worsening of renal function (17). The glomerular filtration rate (GFR) measures the filtration capacity of the kidneys and is considered the best overall index of renal function. The sMDRD formula is an accurate formula for estimating GFR (18).

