### **9.3.2 Coronary angiography**

A coronary angiogram will be obtained at baseline. PCI of the ischemia related artery will be performed if indicated according to current protocols (possibly thrombus aspiration, balloon angioplasty and/or stenting, using bare metal stents or drug eluting stents). After the PCI procedure, a control coronary angiogram will be performed. Intravenously administered nitroglycerine will be given after the procedure and before the last angiogram in all patients.

The following baseline and post-procedural angiographic features will be recorded: Quantitative Coronary Angiography (QCA) data (reference diameter, minimal lumen diameter, and diameter stenosis, lesion length), the presence of thrombus, Thrombolysis In Myocardial Infarction (TIMI) flow grades, myocardial blush grade (MBG), and the presence of distal embolization.

QCA data and TIMI flow grades will be measured as previously described (72;73). The evaluation of MBG will be performed as described by Van 't Hof et al: 0, no myocardial blush; 1, minimal myocardial blush or contrast density; 2, moderate myocardial blush or contrast density, but less than that obtained during angiography of a contra- or ipsilateral non-infarct related coronary artery; and 3, normal myocardial blush or contrast density, comparable with that obtained during angiography of a contra- or ipsilateral non -ischemia-related coronary artery (74). Persisting myocardial blush ("staining") suggests leakage of contrast medium into the extravascular space and is graded 0. Next too MBG evaluation by the interventional cardiologist, MBG may also be assessed using the

Quantifying Blush Evaluator (QuBE), a computer program. QuBE has been demonstrated to provide practical, freely available, computer assessment of myocardial perfusion (75).

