### 9.3.3 Electrocardiography

A standard 12-lead electrocardiogram is acquired at the time of presentation, after the PCI procedure, before hospital discharge, and at each outpatient clinic visit. Mean time interval between pre and post intervention will be registered. The ECG was recorded at a speed of 25 mm/s and a voltage of 10mm/mV. Q and R durations were measured in milliseconds along the PR baseline (1mm = 40ms), and the R amplitude in millivolts (1mm = 0.1 mV). Pre-intervention ECG will be analyzed on the presence of ST-deviation. The post-intervention ECG will be used to score the incidence and location of new Q-waves.

Electrocardiographic criteria of sufficient duration and amplitude for pathologic Q-waves were to meet the lead-specific standards of the Minnesota Code (codes 1-1 through 1-2, except 1-2-8) [Minnesota]. Additionally, the following criteria were used: Q wave  $\geq 30$ ms on lead aVF, Q wave  $\geq 30$  ms on leads I and aVL, Q wave  $\geq 30$  ms in  $\geq 2$  on leads V4 to V6, R wave  $\geq 40$  ms in lead V1, any Q wave in lead V2, and R wave  $\leq 0.1$  mV and  $\leq 10$  ms on lead V2 according to Selvester's QRS screening criteria for Q-wave myocardial infarction.

Two observers blinded to study randomization will analyze all ECG recordings.

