### **11.3 Sample size**

The study is powered for the supposed change caused by the intervention in global left ventricular ejection fraction between the intervention group and placebo group at 4 months after hospitalization. This trial is primarily intended as a proof of concept study, and therefore not powered for a mortality benefit, but for the surrogate endpoint difference in left ventricular ejection fraction measured with CMR imaging 4 months after primary PCI. Van der Vleuten et al (8) demonstrated that a decrease of 5% in LVEF after STEMI leads to a HR of 1.44 for mortality at 1 year follow-up. The recently published HEBE III trial assumed a 3% change in LVEF to be clinical relevant

and to be feasible. Therefore a difference of 3% in LVEF is a relevant primary endpoint. With 141 patients in each study group, the study has 80% power to detect a 3% difference in change in ejection fraction between active treatment and control, assuming a 2-sided  $\alpha$  of .05 for the change in left ventricular ejection fraction.

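### Section 11.1 names two unranked analyses for LVEF; the adjusted one cannot be run, and the t-test that remains ignores pre-dose predictors already collected.

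*Protocol*

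**What the plan says.** The primary endpoint is LVEF by CMR at 4 months, compared between arms by intention to treat (9.1.1). Section 11.1 offers two analyses that could apply to it.

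- A general sentence on means: "Differences between group means will be assessed with the two-tailed Student's t-test". LVEF is not singled out.
- A sentence that does name the primary endpoint: linear regression on metformin use, with the later value adjusted for the value at baseline.

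Nothing says which of these decides the trial. The only other adjustment in 11.1 is attached to the Cox model, used "to calculate relative risks and to adjust for differences in baseline characteristics". The threshold is common to all tests: "Statistical significance is considered as a two-tailed p value <0.05".

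Section 11.3 states that with 141 patients per group "the study has 80% power to detect a 3% difference in change in ejection fraction between active treatment and control". The formula in 11.3.1 is for two unadjusted means and has no covariate or correlation term.

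Several variables are fixed before the first dose, which comes within 3 hours after PCI (5.1):

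- age, symptom-onset time and admission time (9.3.1);
- angiographic data, where "The following baseline and post-procedural angiographic features will be recorded", including TIMI flow and blush grade (9.3.2);
- the presenting ECG: "Pre-intervention ECG will be analyzed on the presence of ST-deviation" (9.3.3);
- "location of myocardial infarction", which appears only as a subgroup factor (9.2).

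None of them is named as a covariate for LVEF.

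**The concern.** A reader of 11.1 could think that the LVEF analysis is already adjusted. In practice it is not: the one covariate named for it does not exist, and the covariates that do exist are not named. Whatever variance they explain stays in the error term, so the confidence interval is wider than it need be in a trial planned at 80% power with no reserve. Randomisation in section 6.1 uses blocks of 6 and mentions no strata, so the design does not balance these factors either. Because the two analyses are unranked, the choice of primary analysis also stays open until someone finds that one of them cannot be fitted.

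**Working it through.** **1. Can both analyses be run for LVEF?** Section 9.3.6 places the CMR at 4 months after PCI, and the visit list in 9.4 has a CMR at T3 and none at T0. No baseline CMR-LVEF exists, so the regression as worded has no baseline value to adjust for. The GEE analysis in 11.1 is for repeated measurements and does not fit an endpoint measured once. That leaves the t-test.

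**2. The plan's own figure.** Inputs from 11.3.1: A = 1.96, B = 0.84, SD 9, difference 3.

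N = (1.96 + 0.84)² × 2 × (9²/3²) = 7.84 × 18 = 141.12, against 141 stated. It reproduces (142 if rounded up).

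Evaluable patients: 380 × (1 − 0.26) = 281.2, or about 140.6 per arm. There is no margin above the required number.

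**3. Power and precision of the unadjusted test at 141 per arm.**

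- Standard error = 9 × √(2/141) = 1.072.
- Normal approximation: Φ(3/1.072 − 1.96) = Φ(0.839) = 79.9%. The noncentral t gives 79.7%.
- 95% CI half-width = 1.96 × 1.072 = 2.10 LVEF points.

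**4. The same with covariates.** If pre-dose covariates explain a share R² of the variance of 4-month LVEF, the residual SD is 9 × √(1 − R²). The protocol gives no R², so the values below are assumed.

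| R² | Residual SD | Power, normal | Power, noncentral t | CI half-width | Difference detectable at 80% |
|---|---|---|---|---|---|
| 0 | 9.00 | 79.9% | 79.7% | 2.10 | 3.00 |
| 0.05 | 8.77 | 81.9% | 81.6% | 2.05 | 2.93 |
| 0.10 | 8.54 | 83.9% | 83.7% | 1.99 | 2.85 |
| 0.20 | 8.05 | 87.9% | 87.7% | 1.88 | 2.69 |
| 0.30 | 7.53 | 91.7% | 91.5% | 1.76 | 2.51 |

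A gain of about 5 percentage points needs R² of about 0.13 (84.9% by noncentral t).

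**5. A yardstick from the protocol.** Section 10.5 allows recruitment to rise from 380 to at most 450. That lowers the variance of the estimate by 1 − 380/450 = 15.6%. Covariates with R² of about 0.16 would match it without another patient.

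**6. Cost in degrees of freedom.** Four single-term covariates take the residual degrees of freedom from 280 to 276, which is negligible.

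**The case against.** The strongest reply has four parts.

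- **The t-test is sound.** Under randomisation its type I error and interval already allow for chance imbalance, and it matches the sample-size formula. This stands. A reader might infer bias or an invalid test, but nothing in the protocol supports that. The loss is one of efficiency and clarity.
- **Covariate lists belong in the SAP, which is not at hand.** This would settle the matter if the protocol had left the analysis open. It did not: it names a test, sizes the trial on it, and names an adjusted model that its own visit schedule rules out. Echocardiography at T0 does not supply the missing value. It is a different measurement, listed in 9.4 for diastolic function. Systolic parameters during hospitalisation are named in 2.2 and 9.1.3, but they are not stated to precede the first dose.
- **The gain may be small.** This stands as a caution. With R² of 0.05 the gain is about 2 percentage points. Eligibility (first infarction, post-PCI TIMI 2/3, stent of at least 3.0 mm) may narrow the prognostic spread. Section 11.3 also speaks of a difference in change, so it is not clear that the SD of 9 describes the raw 4-month value.
- **Not every attractive covariate is shown to be collected.** This stands. The Rationale says "The presence of multi-vessel disease is also associated with a limited recovery of myocardial function after MI", but in a paragraph mainly about diabetic patients, who are excluded. Multi-vessel disease is not listed by name among the recorded features, although both coronary arteries are visualised (7.2). Time of PCI is not listed by name either.

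**Conclusion.** The point holds as one of efficiency and clarity. Section 11.1 names two analyses for the primary endpoint without ranking them, and the adjusted one cannot be carried out for CMR-LVEF. The unadjusted t-test that remains is valid and delivers about 80% power, but it omits plausible pre-dose predictors that the protocol already lists. The possible gain runs from about 2 percentage points (R² 0.05) to about 12 (R² 0.30), given SD 9, a difference of 3 and 141 evaluable patients per arm. The R² range is an assumption.

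Three stronger readings go beyond the text:

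- That these are strong predictors of 4-month LVEF: the protocol gives no R² or correlation.
- That no adjustment of the primary endpoint was intended: the regression sentence shows that it was.
- That the Cox wording selects covariates by observed imbalance: the text does not say how they are chosen.

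**What to change.** In 11.1, before unblinding:

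- State one primary analysis: a linear model of 4-month CMR-LVEF on treatment and a short fixed list of pre-dose covariates. Examples are infarct location (anterior or not), TIMI flow before PCI, age, and time from symptom onset to admission.
- Add multi-vessel disease only if it is confirmed to be recorded from the index angiogram.
- Do not use enzymatic infarct size as a covariate. Its sampling runs over 24 to 36 hours (9.3.4.1), so most of it follows the first dose.
- Keep the two-sample t-test as a sensitivity analysis.
- Remove the adjustment for baseline outcome where the outcome is CMR-LVEF.

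The cost is a sentence or two of text, a few degrees of freedom, and simple imputation of missing covariate values. The variables in the example list call for no additional patients, visits or measurements.
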